### 9.2.1. Analysis of Primary Endpoint

The primary efficacy endpoint of the trial is the presence of subjects with a sub-optimal pregnancy outcome defined as any of the following: live-borne neonate (singleton) with low birth-weight (or LBW for short, defined as live birth weight <2,500g), premature births (<37 weeks), abortion (≤28 weeks), still birth (>28 weeks), lost to follow-up prior to termination of pregnancy or delivery, or missing birth weight of the neonate. The primary analysis set will be the ITT, and will exclude multiple gestations. Secondary analyses will also be repeated using the per protocol analysis set.

Percentage of subjects with sub-optimal pregnancy outcome will be estimated for each treatment group. The following descriptive statistics will be available:

- Sample size (n) per group;
- Number of subjects with sub-optimal pregnancy outcome (m);
- Proportion of subjects with sub-optimal pregnancy outcome:

$$\hat{p} = \frac{m}{n}$$

- Two sided CI will be formed for the proportion of subjects using the normal approximation to the binomial:

$$\hat{p} \pm z_{1-\alpha/2} \sqrt{\frac{\hat{p}(1-\hat{p})}{n}}$$

The final results will be expressed in percentages, ie, proportions x 100. If the lower confidence limit is <0, it will be set to 0. If the upper confidence limit is >100%, it will be set to 100%.

The Mantel-Haenszel estimate of the common risk ratio will be computed using SAS Proc Freq, adjusted for the randomization strata. The risk ratio will be the proportion of AZCQ subjects with sub-optimal pregnancy outcome over the proportion of SP subjects with sub-optimal pregnancy outcome. The estimated variance for  $\ln(RR_{MH})$  given by Greenland and Robins will be utilized. The two-sided p-value will be calculated using the Wald test statistic on the natural log risk ratio scale.

Additional analysis models for the primary endpoint will be used to examine the interaction of a range of effects with treatment group. These effects include randomization strata, HIV status at baseline, age, and country. An alpha level of 0.05 2-sided will be used for these additional analyses.

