### **Statistical Methods**

#### Sample Size

One blinded sample size assessment will be performed when approximately 1,000 subjects achieve the primary endpoint. The sample size will range between 2,602 and 5,044. Due to the adaptive nature of the sample size determination, operating characteristics of the study design in terms of power and Type I error rate were evaluated using simulations. The design assumed a 20% risk reduction in the primary endpoint of proportion of subjects with sub-optimal pregnancy outcomes (relative risk =0.80, AZCQ/SP),  $\alpha = 0.000625$  1-sided, and provides approximately 90% power. The secondary endpoints such as low birth weight will use an  $\alpha = 0.025$  1-sided. See Section 9.1 for details.

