## 5. STUDY TREATMENTS

The Study treatment is a fixed dose tablet formulation of AZ and CQ (AZCQ) containing 250 mg AZ and 155 mg CQ base. Comparator drug is SP and will be supplied as Fansidar® (Roche) tablet (500 mg sulfadoxine/25 mg pyrimethamine). Subjects will be randomized in 1:1 ratio to receive either AZCQ or SP IPTp regimens. Both regimens will consist of three treatment courses. The treatment courses of AZCQ and SP will consist of the following:

1. **AZCQ treatment course:** 1000 mg AZ and 620 mg of CQ base (4 combination tablets of AZCQ with individual strength of 250 mg/155 mg), by mouth (PO) once daily for 3 days (Days 0, 1, 2);

OR

2. **SP treatment course:** 1500 mg sulfadoxine and 75 mg pyrimethamine (3 fixed tablets of SP strength at 500 mg/25 mg), PO single dose once daily on Day 0.

Each subject will receive three IPTp treatment courses of AZCQ or SP during ANC visits at 4 - 8 week intervals. The first treatment course will be administered during the second trimester (14-26 weeks of gestation as confirmed by ultrasound). The last treatment course should be given to subjects prior to or during 36 weeks of gestation.

The first dose of each AZCQ treatment course will be administered under supervision during the ANC visits. Subsequent two doses of AZCQ will be administered at home under supervision by the fieldworker(s).

Each dose of SP treatment will be administered under supervision during the ANC visits.

Please note that the terms course and dose are often used synonymously in IPTp studies using SP because only one directly observed dose is required per treatment course. Within this protocol, dose represents medications taken on a given day; course means all medications required for a complete treatment at one visit.

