**Table 4. Sample Size Determination**

| Observed Pooled Proportion for The Primary Endpoint at N=1000 | $\leq 0.28$ | $>0.28$ to $\leq 0.32$ | $>0.32$ to $\leq 0.36$ | $>0.36$ to $\leq 0.40$ | $>0.40$ |
|---------------------------------------------------------------|-------------|------------------------|------------------------|------------------------|---------|
| Total Sample Size Required                                    | 5044        | 4206                   | 3552                   | 3030                   | 2602    |

Note that the total sample size required is calculated by employing a group sequential design as detailed in Section 9.5 with the upper bound of each interval assumed to be the true underlying proportion for the SP group.

Due to the adaptive nature of the sample size determination, operating characteristics of the study design in terms of power and Type I error rate were evaluated using simulations. Probabilities for early stopping for efficacy and futility at each of the interim analyses were evaluated as well. The design assumed a 20% risk reduction in the primary endpoint (relative risk=0.80, AZCQ/SP). A 23% risk reduction (relative risk=0.77, AZCQ/SP) was assumed for LBW (key secondary) given that early stopping for efficacy will only occur if both endpoints are positive. Type I error rates were simulated under the null hypothesis of no difference. Each scenario under the alternative hypothesis was run with 100,000 simulation iterations. One million iterations were used under the null hypothesis for each stated true proportion, for the primary endpoint.

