## 9.2. Efficacy Analysis

The primary efficacy analysis population (ie, Primary Analysis Set) will be intent-to-treat (ITT) for all endpoints. It will consist of subjects who are randomized, have received at least one dose of study medication (Day 0 at Visit 1 is considered the first dose of study medication), and have a single fetus. Subjects without the required data needed to compute an endpoint will be treated as missing. Analyses will also be performed for as per protocol analysis set, considered secondary. A per protocol analysis set will consist of all ITT subjects who have been compliant with study medication and will exclude subjects who have a neonate birth-weight measured greater than 7 days after birth if they do not already meet the definition of sub-optimal pregnancy outcome, and also exclude subjects who withdraw from study drug and switch to standard of care IPTp treatment. Compliance with study medication will consist of at least 6 of the 9 AZCQ daily doses, and at least 2 of the 3 SP daily doses. Once again, subjects without the required data needed to compute an endpoint will be treated as missing. Sensitivity analyses will be defined for both the ITT and PP populations.

Treatment group comparisons for the primary endpoint will use an overall alpha level of 0.00125 2-sided (equivalent to 0.000625 1-sided), subject to the alpha spending function specified in Section 9.5. Treatment group comparisons for the secondary endpoints will use an overall alpha level of 0.05 2-sided (equivalent to 0.025 1-sided), also subject to the same alpha spending function.

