### 9.2.2. Analysis of Secondary Endpoints

The proportion of subjects with LBW is a key secondary endpoint. It is defined as the following: live-borne neonate (singleton) low birth-weight (or LBW for short, defined as live birth weight <2,500g). A secondary analysis will also be repeated using the per protocol analysis set.

All secondary efficacy endpoints that are dichotomous, expressed as a proportion, will be summarized and analyzed using the same methods as for the primary endpoint. Secondary efficacy endpoints that are not dichotomous will be analyzed using analysis of covariance (ANCOVA) when a baseline value is available, and analysis of variance (ANOVA) otherwise. The ANCOVA model will contain baseline as a covariate, as well as factors for treatment group and randomization strata. The ANOVA model will contain factors for treatment group and randomization strata.

For subjects with nasopharyngeal swabs positive for macrolide resistant and penicillin resistant *Strep. pneumoniae* (to be performed in about 600 subjects in each AZCQ arm and SP arm from at least 2 sites), the proportion positive at Baseline, Day 28-42 post delivery, and at 6 months post last AZCQ IPTp course will be computed. A listing of these subjects will also be provided.

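### For secondary endpoints with zero or very few events in an arm, the normal-approximation interval collapses and the Wald test on the log risk ratio cannot be computed

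*Protocol*

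**What the plan says.** Section 9.2.1 is written for the primary composite. For each arm it gives the size n, the count m, the proportion p̂ = m/n and an interval: "Two sided CI will be formed for the proportion of subjects using the normal approximation to the binomial". The printed formula is p̂ ± z·√(p̂(1−p̂)/n). The only boundary rule is truncation: "If the lower confidence limit is <0, it will be set to 0", with the matching rule at 100%. The comparison uses the Mantel-Haenszel risk ratio adjusted for the randomization strata, the Greenland-Robins variance of its logarithm, and a Wald test on the log scale.

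Section 9.2.2 extends all of this: "All secondary efficacy endpoints that are dichotomous, expressed as a proportion, will be summarized and analyzed using the same methods as for the primary endpoint". No exact or score alternative and no zero-count rule is given. The endpoints in section 2.2 that fall under the sentence include ophthalmia neonatorum, cord blood parasitemia, perinatal or neonatal death, congenital abnormalities, single infections and resistant *S. pneumoniae* carriage. For the swab endpoint, section 9.2.2 separately mentions only the proportion positive at each time point and a listing.

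On levels, section 9.2 says "Treatment group comparisons for the secondary endpoints will use an overall alpha level of 0.05 2-sided" and "Treatment group comparisons for the primary endpoint will use an overall alpha level of 0.00125 2-sided (equivalent to 0.000625 1-sided"). The level of the single-arm interval is not fixed.

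**The concern.** The formula suits a composite expected in roughly 22% to 44% of subjects. It does not suit an outcome seen in no subject or only a few. At p̂ = 0 the estimated standard error is zero, so the interval claims certainty that the rate is nil. Truncation removes impossible negative limits but cannot widen an interval.

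The carried-over test has a parallel problem: the logarithm of the risk ratio does not exist when an arm has no events. The plan would then give no p-value in a split such as 0 against 8, where the contrast is at its most extreme. If nothing is fixed beforehand, the substitute would be chosen after the counts are known.

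**Working it through.** **Inputs.** The protocol summary says "The sample size will range between 2,602 and 5,044", and section 5 says "Subjects will be randomized in 1:1 ratio to receive either AZCQ or SP IPTp regimens". Arms therefore hold 2,602/2 = 1,301 to 5,044/2 = 2,522 subjects. About 600 per arm are swabbed (section 2.2). A 95% interval is assumed, in line with the secondary alpha. The full-arm sizes are upper bounds for some endpoints, because cord blood is taken only at hospital delivery.

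**The plan's own sample sizes first.** Section 9.1 states "The design assumed a 20% risk reduction in the primary endpoint (relative risk=0.80, AZCQ/SP"). On the log risk ratio scale:

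N = 2·(z₁₋α + z₁₋β)²·[(1−p₁)/p₁ + (1−p₂)/p₂]/(ln 0.80)²

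With one-sided α = 0.000625 and 90% power, (3.227 + 1.282)² = 20.33, and (ln 0.80)² = 0.0498. At p₁ = 0.28 and p₂ = 0.224 the bracket is 2.571 + 3.464 = 6.036, so N = 4,928. Multiplying by a group-sequential inflation of 1.0265 gives 5,059, against 5,044 in Table 4. The other classes give 4,217, 3,562, 3,038 and 2,610, against 4,206, 3,552, 3,030 and 2,602. The value 0.44 for the open top class is inferred from the spacing. The arm sizes are sound.

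**Zero events.** The printed half-width is z·√(0·1/n) = 0. The exact upper limit is 1 − 0.025^(1/n): 0.61% for n = 600, 0.28% for n = 1,301 and 0.15% for n = 2,522.

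**Two events in 2,522.** p̂ = 0.079%. The printed interval is −0.03% to 0.19%, truncated to 0 to 0.19%. The exact upper limit is 0.29%.

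**Coverage.** This is the sum of binomial probabilities over all counts whose nominal 95% interval contains the true rate. The rates in the table are assumed, because the protocol gives none for ophthalmia neonatorum, cord blood parasitemia or perinatal and neonatal death.

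| True rate | n = 600 | n = 1,301 | n = 2,522 |
|---|---|---|---|
| 0.05% | 25.9% | 47.8% | 71.6% |
| 0.1% | 45.1% | 72.8% | 91.9% |
| 0.2% | 69.8% | 92.5% | 87.3% |
| 0.5% | 79.8% | 88.2% | 92.4% |
| 1% | 93.0% | 94.0% | 93.5% |

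Coverage oscillates with the rate, so single cells should not be over-read. Averaged over rates expecting up to three events, it is 69% to 72% at the three sizes.

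**The swab endpoint.** Section 1.3.2.4.2 cites a community study in Tanzanian children with one erythromycin-resistant isolate in 1,315 + 1,225 + 1,402 = 3,942 swabs. With 600 subjects the expected count is 600/3,942 = 0.15, and P(no events) = (1 − 1/3,942)^600 = 85.9%. Coverage is 14.1% for the printed interval, 85.9% for Wilson and 99.0% for Clopper-Pearson. This rate may not hold after azithromycin. The same section cites an Australian study with 10 of 37 isolates not sensitive two months after treatment. With the Tanzanian two-month carriage of 149/1,225, that would be (10/37)·(149/1,225) = 3.3%, about 20 events in 600, where coverage is 94.8%. The failure is therefore most likely at baseline or in the SP arm.

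**The comparison.** RR_MH is a ratio of two sums over strata, one weighting AZCQ events and one weighting SP events. With no AZCQ events RR_MH = 0, its logarithm does not exist and the Greenland-Robins variance divides by zero. With no SP events RR_MH itself is undefined. A zero in only one gravidity stratum does no harm. For scale, Fisher's unstratified exact two-sided p-value is 0.031 for 0 against 6 and 0.008 for 0 against 8, at either full arm size. The planned test returns nothing in both cases.

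**Endpoints that are not affected.** At 1.7%, the lowest single-infection prevalence in section 1.3.2.3, coverage is 94.5% (n = 1,301) and 95.0% (n = 2,522). At the 2.95% malformation rate in section 1.3.2.4.1 it is 93.9% and 94.5%. For the primary endpoint at 22% to 44% it is 94.6% to 95.2%.

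**The case against.** The strongest reply is that this is a descriptive line beside m and n, so a reader who sees 0 of 2,522 can supply the uncertainty. Section 9 also leaves detailed methodology to the SAP and lets it modify these plans. Both points limit the weight of the finding. They do not remove it, because the protocol does not leave the method open. It prints a formula and a test and assigns them to all dichotomous secondary endpoints, and the missing p-value is more than a descriptive matter.

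A reader might infer that every uncommon secondary outcome is affected, including congenital abnormality and single sexually transmitted infections. The cited rates contradict that. Rates on treatment could be lower, but the protocol gives no such figures.

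A reader might also infer that the fetal and neonatal safety conclusions rest on these intervals. They do not rest on them alone: neonatal death, stillbirth, spontaneous abortion and congenital anomaly are reported as serious adverse events (sections 8.9 and 8.12.1), safety data are tabulated and listed (section 9.4), and an external committee reviews them (section 9.6).

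Finally, the swab endpoint may fall outside the rule, because section 9.2.2 gives it its own, purely descriptive sentence. That reading is possible. The endpoint is nevertheless a listed dichotomous secondary endpoint, and the general sentence makes no exception.

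**Conclusion.** The point holds for endpoints with zero or very few events in an arm, and only there. The 0-to-0 interval and the failed log risk ratio test follow exactly from the printed method. The loss of coverage is large only when an arm expects roughly three events or fewer: a rate of up to about 0.5% with 600 subjects, 0.2% with 1,301 and 0.1% with 2,522. Over assumed rates of 0.05% to 1%, the tabulated coverage runs from 48% to 94% with 1,301 subjects and from 72% to 94% with 2,522.

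The swab figures rest on one cited study in another population and on applying the general rule to that endpoint. Ophthalmia neonatorum, cord blood parasitemia and perinatal or neonatal death may be affected, but the protocol gives no rates with which to say so. All coverage figures assume a 95% level. This is a minor point of analysis wording: the primary endpoint, the stopping rules and the sample size do not change.

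**What to change.** In section 9.2.2, or in the SAP where section 9 allows it, use Clopper-Pearson intervals for single-arm proportions of secondary endpoints and state their level. Wilson intervals are acceptable except at the very lowest rates, as the 85.9% at 1 in 3,942 shows.

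For the between-arm comparison, prespecify a stratified exact test with an exact or score interval for use when an arm has zero or very few events. Keep the gravidity strata, and fix the count that triggers the switch before any unblinded look; the protocol offers no basis for a particular threshold. State whether the swab endpoint falls under the general rule.

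The cost is wording and a standard programming option. The one downside is that Clopper-Pearson intervals are slightly conservative: at a true rate of 0.1% they cover 98.9% with 1,301 subjects and 98.5% with 2,522.

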#### **4.3. Randomization Criteria**

A computer-generated randomization list will be provided by the sponsor to the investigators. Randomization will be stratified according to gravidae (primigravidae & secundigravidae vs. other gravidae). Among all gravida, approximately 50% subjects will be stratified with primigravidae & secundigravidae. The investigator will assign subject identification numbers sequentially as they are determined to be eligible for treatment (PID numbers). This unique PID number will be retained throughout the study and must appear on all case report form (CRF) pages, source documents and lab data. The eligible subjects who have met all inclusion/exclusion criteria will receive study medication assigned to the next available randomization number at the Day 0 during the first study visit. The randomization number will also be recorded on the proper CRF page.

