#### **9.1. Sample Size and Power Determination**

Sample size will be determined using the observed primary endpoint pooled across both arms following a blinded review when approximately 1000 subjects achieve the primary endpoint.

The underlying true incidence of the primary endpoint in the control group is unknown, but has a substantial impact on the required sample size. To manage the uncertainty, the proportion of subjects experiencing a sub-optimal pregnancy outcome will be estimated from the current trial, when approximately 1000 subjects achieve the endpoint. This evaluation will be done in a blinded manner by the Sponsor study team, though the trial is open label. The underlying incidence will be estimated by the pooled (blinded) overall proportion of subjects experiencing a sub-optimal pregnancy outcome without regard to treatment group.

Total sample size will be determined using Table 4. For example, if the observed proportion of subjects experiencing a sub-optimal pregnancy outcome is found to be 0.30, then the total sample size will be 4206.

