#### 9.5. Interim Analysis

The study will employ a group sequential design with three unblinded analyses conducted at 50%, 70% and 100% of information time (percentage of subjects with data for the primary endpoint). Group sequential stopping rules will be used to stop the trial early for efficacy and futility (futility is non binding) at each of the 2 sequential analyses.

The overall alpha level will be 1-sided 0.000625 and the power will be approximately 90% (See Section 9.1) for establishing superiority of AZCQ over SP in proportion of subjects with sub-optimal pregnancy outcome (primary endpoint). Secondary efficacy endpoints will use an overall alpha level of 1-sided 0.025. The study was designed using the EAST software Version 5.1.

To protect the Type I error rate, the gamma (-4) function will be used for alpha spending for all efficacy endpoints. Similarly, the gamma (-6) function will be used for beta spending for the primary endpoint only. Early stopping for efficacy will only occur if both the proportion of subjects with sub-optimal pregnancy outcome (primary endpoint) and the proportion of subjects with LBW (key secondary) is statistically significantly lower in the AZCQ group compared to SP, as evaluated by the relative risk (primary analysis). Early stopping for futility will only be based on the primary endpoint.

The EAST software will be used to monitor the sequential analyses. It is important to note that the critical values for the stopping boundaries will depend on the percentage of subjects actually in each sequential analysis (the actual observed percentage of information). The new critical values will be calculated within EAST subject to the pre-defined alpha and beta spending functions specified for the design, in order to maintain the appropriate overall power and significance level.

090177e1811dafca\Approved\Approved On: 22-Feb-2010 14:41

The sequential analyses will use unblinded treatment codes, and be prepared by a group within Pfizer but external to the study team. An Independent Data Monitoring Committee (IDMC) external to Pfizer will then be used to formally make decisions on stopping or continuing the study based on the interim results, the predefined stopping regions, and the interim monitoring output from EAST. The membership of the IDMC and its charter, as well as the procedures for performing the interim analyses will be finalized and documented prior to the first interim analysis.

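### Country is recorded but does not enter the primary Mantel-Haenszel risk ratio; adding it as a stratum is an optional, nearly free gain in precision

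*Protocol*

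**What the plan says.** Protocol Section 4.3: "Randomization will be stratified according to gravidae", in two groups (first and second pregnancies against all others), with about half of the subjects in the first group. No other stratification factor is named.

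Protocol Section 9.2.1: the Mantel-Haenszel estimate "of the common risk ratio will be computed using SAS Proc Freq, adjusted for the randomization strata". The variance is that of Greenland and Robins, and the p-value comes from a Wald test on the log scale. The strata of the primary analysis are therefore the two gravidity groups.

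The same section plans additional models for interaction with treatment, at two-sided 0.05: "These effects include randomization strata, HIV status at baseline, age, and country". This is the only analysis in Section 9.2.1 that uses country.

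Section 9.2.2 carries the primary method over to every dichotomous secondary endpoint, including low birth weight. Section 9 allows the SAP to modify the plan, but requires a major change to the primary analysis to appear in a protocol amendment as well.

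**The concern.** The trial runs in several countries, and the background gives reasons to expect risk to differ between them. Section 1.2 describes SP resistance that varies by region. Section 1.4.2.2 reports that chloroquine sensitivity returned more slowly in Kenya than in Malawi. Section 1.3.2.3 gives wide ranges for antenatal STI prevalence across sub-Saharan Africa, for example 5.3 to 20.8% for *C. trachomatis*. Loss to follow-up and missing birth weight count as failures in the primary endpoint, and both depend on local follow-up and on how often women deliver at home.

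If country predicts the outcome, strata that include it reduce the variance of the log risk ratio and remove any chance imbalance between arms in country from the estimate. An interaction model reported alongside does neither for the primary test. What is at stake is a modest amount of precision. Type I error and the stated power are not in question.

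**Working it through.** **Inputs from the protocol**
- Alpha and power (Section 9.5): "The overall alpha level will be 1-sided 0.000625 and the power will be approximately 90" percent.
- Effect (Section 9.1): "The design assumed a 20% risk reduction in the primary endpoint (relative risk=0.80, AZCQ/SP").
- SP rate behind each Table 4 entry: "with the upper bound of each interval assumed to be the true underlying proportion for the SP group".
- Worked example (Section 9.1), observed pooled proportion 0.30: "then the total sample size will be 4206". The interval's upper bound, hence the SP rate used, is 0.32.
- Allocation (Section 5): "Subjects will be randomized in 1:1 ratio to receive either AZCQ or SP IPTp regimens".
- Looks at 50%, 70% and 100%; gamma(-4) alpha spending; non-binding gamma(-6) beta spending (Section 9.5).

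**Step 1: reproduce the sample size.** The spending function gives Z bounds of 3.793, 3.652 and 3.283. The drift needed for 90% power with the futility spending is 4.560. For the unstratified log risk ratio,

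n per arm = [(1-p0)/p0 + (1-p1)/p1] x drift² / (ln 0.8)².

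With p0 = 0.32 and p1 = 0.256, this is (2.125 + 2.906) x 20.80 / 0.04979, about 2,102 per arm or 4,204 in total, against 4,206 stated. The five Table 4 columns come out as 5,042 / 4,204 / 3,552 / 3,030 / 2,602, against 5,044 / 4,206 / 3,552 / 3,030 / 2,602. The last column uses an SP rate of 0.44, inferred from the Table 5 grid. At 4,206 the unadjusted power is about 90.2%. The stated power therefore relies on no covariate adjustment.

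**Step 2: variance with strata.** With equal arms in every stratum and a common risk ratio of 0.80, the expected Greenland-Robins variance reduces to

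Var(ln RR) = [1.8 m - 1.6 (m² + V)] / (0.8 n m²),

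where m is the mean SP rate, V the variance of the SP rate between strata and n the number per arm. With m = 0.32 and n = 2,103, the denominator is 0.08192 x 2,103 = 172.28.

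- No strata, V = 0: numerator 0.576 - 0.16384 = 0.41216, SE 0.04891.
- Gravidity strata, assuming rates 4 points above and below the mean (V = 0.0016): numerator 0.40960, SE 0.04876. This is the planned analysis and the right baseline.

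**Step 3: add country.** Assume six equal countries with evenly spaced SP rates. With spacing d, the between-country variance is d² x 35/12, and the fall in variance relative to the plan is 1.6 x (d² x 35/12) / 0.40960.

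| Country SP rates | d | Between-country variance | SE | Fall in variance | Power |
|---|---|---|---|---|---|
| all 0.32 | 0 | 0 | 0.04876 | 0% | 90.4% |
| 0.28-0.36 | 0.016 | 0.00075 | 0.04869 | 0.3% | 90.5% |
| 0.24-0.40 | 0.032 | 0.00299 | 0.04847 | 1.2% | 90.9% |
| 0.20-0.44 | 0.048 | 0.00672 | 0.04812 | 2.6% | 91.4% |

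Power is for the three-look design with the bounds above and no futility stop, at drift |ln 0.8| / SE. It is conditional on 4,206 subjects. Table 5 shows 92% at an SP rate of 0.32 because its sample size varies with the blinded pooled rate.

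The variance reductions correspond to about 12, 49 and 110 of 4,206 subjects (4,206 x 0.0029, 0.0117 and 0.0263). They express precision only: the enrolled number is set by Table 4, so nobody is spared enrolment. With six countries the twelve cells would hold about 350 women each (4,206 / 12), which is far from sparse.

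**The case against.** The strongest case against is that nothing is wrong. Analysing by the randomization strata is valid and matches the design, Sections 4.3 and 9.2.1 agree, and the sample size already delivers about 90% power unadjusted at the strict alpha. Section 9.2 also promises sensitivity analyses, and a country-adjusted one could sit in a SAP that is not shown. All of this stands, and it is why the point is an option and not a defect. What remains is that the protocol itself fixes the strata of the primary test, and a supportive analysis elsewhere does not sharpen that test.

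Three stronger readings are tempting, and the protocol does not support them.

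- **That country is ignored.** It is named among the effects to be examined for interaction with treatment. It is only absent from the primary estimate.
- **That Table 5, which runs from 0.24 to 0.44, shows how far countries differ.** Those rows are scenarios for one unknown overall SP rate. Even if they were country rates, the largest possible SD around a mean of 0.32 would be sqrt(0.08 x 0.12) = 0.098, so larger gains based on, say, an SD of 0.12 cannot be drawn from that table. A variance reduction of about 7% needs country rates running from 0.12 to 0.52, for which the protocol gives no ground.
- **That the randomization must be restratified because country may be imbalanced.** Section 4.3 does not say whether the lists are separate by site. If they are, country is already roughly balanced and the gravidity-only variance is slightly conservative. If they are not, country strata in the analysis deal with chance imbalance.

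**Conclusion.** The point holds as an optional improvement. The primary Mantel-Haenszel risk ratio uses two gravidity strata and leaves out a recorded baseline factor that plausibly predicts the outcome. The gain is small: about 0.3% to 2.6% in the variance of the log risk ratio and roughly 0.1 to 1.0 point of power for country SP rates spread over 8 to 24 percentage points, and zero if country is not prognostic. These figures rest on assumed country rates, six equal countries, a gravidity effect of 4 points either way and a common risk ratio of 0.80. That country is prognostic is an inference from the background sections, since no country rate is reported. The planned analysis remains valid as written.

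The change is still worth making because it costs almost nothing and also reaches low birth weight. That endpoint must be positive too for early efficacy stopping (Section 9.5), and its stated power is only about 82% to 88% (Section 9.1.1). The gain for low birth weight was not calculated.

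**What to change.** In Section 9.2.1, define the strata of the primary Mantel-Haenszel risk ratio as gravidity group x country, and apply the same strata to the dichotomous secondary analyses in Section 9.2.2, including low birth weight. Keep the gravidity-only risk ratio as a prespecified sensitivity analysis. Fix the change before any unblinded look, the first of which is at 50% information, and, because Section 9 calls for it if the change counts as major, carry it in a protocol amendment as well as in the SAP.

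The cost is a sentence or two of text and one more variable in the TABLES statement of the same SAS procedure. The variance estimator already specified suits the extra strata. Randomization, sample size and alpha spending stay as they are.
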